### 9.5.2 Analysis of clearance of cervical HPV infections

|                                                           | Covariates                                  | Type    | Categories                                                                                                                                                                             | Time-dependent | Comment                      |
|-----------------------------------------------------------|---------------------------------------------|---------|----------------------------------------------------------------------------------------------------------------------------------------------------------------------------------------|----------------|------------------------------|
| Main covariate                                            | HPV type                                    | Class   | HPV 16
HVP 18
HPV 31
HVP 33
HPV 45
Other high risk HPV type (35, 39, 51, 52, 56, 58, 59, 66, 68)
Other low risk HPV type (6,11, 34, 40, 42, 43, 44, 53, 54, 70, 74 ) | No             | Main variable of interest    |
| Demographic characteristics
(defined at subject level) | Region                                      | Class   | Europe
Asia Pacific
Latin America
North America                                                                                                                               | No             |                              |
| Behavioral Covariates
(defined at subject level)       | Smoking                                     | Ordinal | [0-0.5[ pack/year
≥0.5 pack/year                                                                                                                                                    | No             | Re-assessed at yearly visits |
|                                                           | Age at beginning of sexual activity (years) | Ordinal | Never had sexual intercourse
<15
15-17
18-25                                                                                                                                  | No             |                              |

|                     | Covariates                                                                     | Type    | Categories                                                                          | Time-dependent | Comment                      |
|---------------------|--------------------------------------------------------------------------------|---------|-------------------------------------------------------------------------------------|----------------|------------------------------|
|                     | Number sexual partner during the previous year                                 | Ordinal | 0
1
2-3
≥4                                                                 | No             | Re-assessed at yearly visits |
|                     | Marital status                                                                 | Binary  | Living or lived with a partner
Single                                            | No             | Re-assessed at yearly visits |
|                     | At least one previous pregnancy                                                | Binary  | No
Yes                                                                           | No             | Re-assessed at each visit    |
|                     | Hormones for contraception or another indication                               | Binary  | No
Yes                                                                           | No             | Re-assessed at each visit    |
|                     | Intra-uterine device                                                           | Binary  | No
Yes                                                                           | No             | Re-assessed at each visit    |
|                     | Sterilized                                                                     | Binary  | No
Yes                                                                           | No             | Re-assessed at each visit    |
|                     | Chlamydia trachomatis                                                   | Binary  | No
Yes                                                                           | No             | Re-assessed at each visit    |
| Clinical covariates | Previous cervical HPV infection                                         | Class   | No
Yes, with at least one high risk HPV type
Yes, with only low risk HPV type | No             | Re-assessed at each visit    |
|                     | Co-infection* with other HPV types (concomitant cervical HPV infection) | Class   | No
Yes, with at least one high risk HPV type
Yes, with only low risk HPV type | Yes            | Re-assessed at each visit    |

\* Co-infection with other HPV types is defined as the detection of these HPV types at time of the onset of the reference cervical HPV infection or, if this infection is persistent, during the duration of the reference cervical HPV infection until its end or until the occurrence of the event, whichever comes first.

Consequently any cervical HPV infection which onset is prior to the onset of the reference cervical HPV infection will be considered as a previous cervical HPV infection and any cervical infection which onset if after the end of the reference cervical HPV infection and before the occurrence of the event will not be considered as a co-infection.

However, when analyzed as time-varying covariables, co-infections will be considered until the occurrence of the event (e.g., clearance). Co-infections will be analyzed as time-dependent variable is the Cox regression models (not in the GEE models)

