### 4.4.2 Clinical determinants

For each reference cervical HPV infection with a given HPV type over the 48-month follow-period, the following determinants will be defined:

- HPV type: 16; 18; 31; 33; 45; Other high risk HPV type; Other low risk HPV type.

The above categorization of HPV types will be used in the univariate and multivariable analyses. All HPV types will be considered individually in the tables presenting descriptive statistics by HPV type as well as high risk and low risk categories. The high risk (oncogenic) category is obtained by grouping together HPV types 16, 18, 31, 33, 35, 39, 45, 51, 52, 56, 58, 59, 66, and 68. The low risk (non-oncogenic) category is obtained by grouping together HPV types 6, 11, 34, 40, 42, 43, 44, 53, 54, 70 and 74. In some cases, the category “No cervical HPV infection” will be added in the categorization for univariate and multivariable analyses.

- HPV infection category: 6-month persistent, less than 6-month persistent, transient, last visit detected.
- Previous cervical HPV infection: No; Yes, with at least one high risk HPV type; Yes, with only low risk HPV type.
- Histopathologically-confirmed CIN2+ (or CIN1+, or CIN3+) following the reference cervical HPV infection, associated with a different HPV type, and preceding the CIN2+ (or CIN1+, or CIN3+) associated with the same HPV type as the reference infection (i.e. date of CIN2+ (or CIN1+, or CIN3+) following the reference infection strictly inferior to date of CIN2+ (or CIN1+, or CIN3+) associated with the same HPV type as the reference infection): No; Yes, with at least one high risk HPV type; Yes, with only low risk HPV type.

- Histopathologically-confirmed CIN2+ (or CIN1+, or CIN3+) preceding the reference cervical HPV infection, associated with a different HPV type : No; Yes, with at least one high risk HPV type; Yes, with only low risk HPV type.
- Co-infection with other HPV types (concomitant cervical HPV infections): No; Yes, with at least one high risk HPV type; Yes, with only low risk HPV type.

Co-infection with other HPV types is defined as the detection of these HPV types at time of the onset of the reference cervical HPV infection or, if this infection is persistent, during the duration of the reference cervical HPV infection until its end or until the occurrence of the event, whichever comes first.

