#### 6.2.4.5 Statistical methods

The time between persistent cervical HPV infections and lesions will be analyzed using Kaplan-Meier method and Cox regression models.

Kaplan-Meier curves presenting the cumulative probability of lesions following 6-month persistent cervical HPV infections will be displayed and compared between groups for determinants of interest using the Log-rank test (univariate analyses). Cox regression models will be also performed for the univariate analyses in order to obtain unadjusted hazards ratios of the determinants of interest.

In addition, a multivariable Cox regression model will be performed in order to estimate the relative contribution of each determinant adjusting for the simultaneous effects of the other covariates. The model will include: time-independent covariates (e.g., age and region at study entry), time-independent covariates re-assessed at follow-up visits (e.g., behavioral determinants updated over the follow-up period using the yearly behavioral questionnaires) and time-dependent covariates (e.g., concomitant cervical HPV infections, i.e. co-infection). Also, some of the determinants will be distinguished depending on whether they started

before or after the 6-month persistent cervical HPV infections leading to the lesions in order to differentiate their effects in the pathway leading from cervical HPV infection to lesion (cf. Sections 4.4.2 and 4.4.3 for the definition of behavioral and clinical determinants and Section 8.5.1 for the list of determinants that will be taken into account in the analysis).

As the same subject may contribute to more than one observation (e.g., the same women may have several persistent cervical HPV infections of same or different HPV types leading or not to lesions associated with these HPV types), the analysis will be performed using an appropriate approach (counting process, clustering etc.) carried out either by a standard or a stratified Cox model depending on whether i) the recurrent events may be considered as identical or different and ii) the assumption that the estimated proportional hazards are constant over time is fulfilled or not [Andersen et al., 1993; Prentice et al, 1981; Kelly and Lim, 2000; Kleinbaum and Klein, 2005].

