### 6.2.6.3 Dependent variable

For both definitions of the clearance of cervical HPV infection presented in Section 4.3.1, the clearance of an incident cervical HPV infection will be analyzed by means of a binary variable with the following categories:

- 0 = No clearance of the cervical HPV infection
- 1 = Clearance of the cervical HPV infection

(See Section 4.3.1 and flowchart in Section 8.2 for case definitions and determination of incident cervical HPV infections and their clearance; See Section 8.3.3 for the flowchart of data associated with this objective).

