#### **6.2.6.4 Statistical methods**

The clearance of cervical HPV infections (two definitions) will be analyzed using marginal binary-response models such as generalized estimating equation (GEE) regression models for clustered binary responses [Zeger et al., 1988].

These multivariable analyses will allow taking into account that women may contribute to several observations related to different HPV types, resulting in multiple event times, in addition to estimating the simultaneous effects of determinants. The GEE approach will adjust for the dependency caused by the repeated observations on the same subject by estimating robust standard errors for parameter estimates. The appropriate correlation matrix structure accounting for within-subject correlation will be determined at the time of the statistical analysis based on the patterns observed.

Interactions between determinants of interest and the type of cervical HPV infection will be explored by introducing interaction terms between these determinants and a variable categorizing the type of cervical HPV infections as transient or other, 6-month persistent and 12-month persistent (See Sections 4.4.2 and 4.4.3 for the definition of behavioral and clinical determinants and Section 8.5.2 for the list of determinants that will be taken into account in the analysis). In the presence of strong interactions, the analyses will be stratified according to the type of cervical HPV infection.

Results from the multivariable regression models will include odds ratios (95% CI).

Depending on the results, other models taking into account the time between cervical HPV infections and their clearance (i.e. Cox regression models) may be used also as described in Section 6.4.2.5. In such case, cervical HPV infection detected at the last visit will be excluded of the analysis because they will all be censored at day 0.

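### In the clearance GEE, the window for reading co-infection depends on whether and when the infection cleared, so its odds ratio is biased even if co-infection has no effect

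*SAP*

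**What the plan says.** **Outcome and model.** Section 6.2.6.3 codes each infection 0 or 1, where "1 = Clearance of the cervical HPV infection". Section 6.2.6.4 plans "marginal binary-response models such as generalized estimating equation (GEE) regression models for clustered binary responses" and reports odds ratios. A Cox model of time to clearance is optional, depending on results. Section 9.3.3 states that every infection enters the clearance analysis.

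**Covariate.** Section 4.4.2 gives co-infection three levels: "No; Yes, with at least one high risk HPV type; Yes, with only low risk HPV type". The footnote to Section 9.5.2 sets the basic window: "Co-infection with other HPV types is defined as the detection of these HPV types at time of the onset of the reference cervical HPV infection". It then extends the window: "if this infection is persistent, during the duration of the reference cervical HPV infection until its end or until the occurrence of the event". Types whose onset precedes the reference infection count as previous infection instead.

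**Handling over time.** The Section 9.5.2 table marks co-infection as time-dependent. The footnote limits this: "Co-infections will be analyzed as time-dependent variable is the Cox regression models (not in the GEE models").

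**Infection types.** Under Section 4.3.1 a transient infection is negative at the evaluation six months later. A 6-month persistent infection has uninterrupted positive samples spanning more than 150 days. Under Section 9.2 a type first detected at the last visit is recorded as not cleared.

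**The concern.** Each infection gets one fixed co-infection value in the GEE. An infection that is negative at the next sample is checked for other types once. An infection that stays positive is checked at every visit until it ends or follow-up stops. The switch from one visit to many is triggered by not clearing at the first opportunity, and the window then grows with each further positive sample. An exposure ascertained partly after onset, over a period that the outcome helps to set, is associated with that outcome even when it has no effect on it.

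Infections first seen at the last visit work in the opposite direction, because they have a one-visit window and are always coded as not cleared. The two artefacts partly cancel, in a proportion that has nothing to do with biology.

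At stake is the co-infection odds ratio for clearance, which is one of the determinant effects the SAP sets out to evaluate.

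**Working it through.** The SAP gives no clearance rate, co-infection rate or expected effect for this analysis, so there is no planned figure to reproduce. The check asks what odds ratio (OR) the planned coding returns when the true OR is 1.

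**Inputs from the SAP**
- PCR at Months 0, 6, 12, 18, 24, 30, 36 and 48, so a run holds 1 to 8 positive samples (Section 3.2).
- Onset-only window for a single positive sample and whole-run window for two or more (Section 9.5.2 footnote).
- Last-visit first detections kept and coded as not cleared (Sections 9.2 and 9.3.3).

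**Assumptions (not in the SAP)**
- Probability c that the next sample is negative: 0.3 to 0.6, constant.
- Probability q0 of another type at the onset visit: 0.1 to 0.3.
- Probability q of newly detecting another type at each later positive visit: 0.05 to 0.2.
- Onset over the eight visits either uniform or with double weight on the first and last.
- Co-infection collapsed to yes/no, and clearance taken as one negative sample (Definition 1).

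**Formulas**, for onset at visit o and L = 8 − o + 1 visits remaining including onset
- Run of m < L positives, cleared: probability (1 − c)^(m−1) × c.
- Run of m = L positives, not cleared: probability (1 − c)^(L−1).
- Coded co-infected under the SAP: 1 − (1 − q0)(1 − q)^(m−1). Coded at onset only: q0.
- OR from the 2×2 table. A logistic GEE with this single binary covariate and independence working correlation gives the same point estimate.

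**Step 1: window length alone.** With q0 = 0.2 and q = 0.1, the chance of being coded co-infected is 20% for 1 positive visit, 28% for 2, 35% for 3, 48% for 5 and 62% for 8.

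**Step 2: one scenario in full** (c = 0.4, q0 = 0.2, q = 0.1, uniform onset; shares of all infections)

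| | Co-infected | Not co-infected |
|---|---|---|
| Cleared | 0.1848 | 0.5080 |
| Not cleared | 0.0914 | 0.2158 |

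OR = (0.1848 × 0.2158) / (0.5080 × 0.0914) = 0.86.

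Last-visit onsets are 1/8 = 0.125 of all infections: 0.025 co-infected and 0.100 not, none cleared. Without them the second row is 0.0664 and 0.1158, and OR = (0.1848 × 0.1158) / (0.5080 × 0.0664) = 0.63.

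With double weight on the first and last visits, the cells are 0.1764 and 0.4750 (cleared), 0.0949 and 0.2537 (not cleared). OR = (0.1764 × 0.2537) / (0.4750 × 0.0949) = 0.99. The artefacts cancel by chance of the onset pattern.

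**Step 3: all scenarios** (c = 0.3, 0.4, 0.5, 0.6; true OR = 1)

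| (q0, q) | All infections, uniform onset | All infections, double first/last | Without last-visit onsets, both patterns |
|---|---|---|---|
| (0.2, 0.05), (0.2, 0.1), (0.3, 0.1), (0.3, 0.2) | 0.776–0.964 | 0.935–1.064 | 0.530–0.784 |
| (0.1, 0.1), (0.2, 0.2) | 0.738–0.900 | 0.908–1.087 | 0.481–0.536 |
| (0.3, 0.05) | 0.908–0.975 | 0.966–1.016 | 0.800–0.840 |

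**Step 4: onset-only coding.** The chance of being coded co-infected is q0 in both rows of the table, so OR = 1.00 in every scenario.

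**The case against.** **The bias in the planned analysis may be small.** This stands. Values near 0.5 arise only when last-visit detections are removed, and the SAP removes them only from the optional Cox model, where co-infection is time-dependent anyway. A reader might infer that the planned GEE would roughly halve the odds ratio, or would always make co-infection appear to hinder clearance. Neither follows, because the pooled value lies on either side of 1 depending on the onset distribution.

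**Section 6.2.6.4 provides a safeguard.** It explores interactions with infection type and stratifies if they are strong. Within transient or other infections the window is one visit for all, and the null OR is 1.00. It is also 1.00 among infections with two positive visits, and 0.80 to 0.97 among longer ones. Stratification would therefore remove much of the problem. But it is conditional on a strong interaction, and the unstratified model remains the planned one.

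**Clearance is not duration.** This is correct. A long infection that later clears is coded 1. The link runs through the window: uncleared infections other than last-visit detections tend to have longer windows.

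**The lesion analyses.** A reader might extend the point to the univariate Kaplan-Meier comparisons. Section 6.2.4.5 says curves will be "compared between groups for determinants of interest using the Log-rank test (univariate analyses"), but it does not name co-infection there, and it cites co-infection as a time-dependent covariate in the Cox model. No log-rank test by co-infection is planned, so this would be a problem only if one were added. The primary CIN2+ objective is not shown to be affected.

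**Conclusion.** The point holds for the clearance GEE. A fixed co-infection value read over a window that depends on clearance gives a biased odds ratio when the true effect is nil. For the planned analysis of all infections the null OR is about 0.74 to 1.09. Among infections not first detected at the last visit it is about 0.5 to 0.85.

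These ranges describe the scenarios run and are not bounds. They rest on assumed clearance and detection rates, two assumed onset patterns, constant clearance, a yes/no collapse of the covariate and no adjustment for other determinants. The mechanism does not depend on those rates; the size and the pooled sign do.

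This should be fixed. It does not threaten the plan as a whole: it concerns one covariate in one secondary objective, in which HPV type is the main variable of interest.

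**What to change.** - In Section 9.5.2, define co-infection for the GEE from the sample at onset of the reference infection, for every infection, persistent or not, keeping the three levels.
- Keep the rule that types with earlier onset count as previous infection. If any type present in the onset sample is to count instead, say that the two covariates may overlap.
- Use later detections only as a time-dependent covariate in the Cox model of clearance.
- Align the time-dependent entry in the Section 9.5.2 table with its footnote, for example by stating the GEE and Cox versions separately.
- If co-infection is ever used to group Kaplan-Meier curves or a log-rank test, use the same onset-only definition.

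The cost is a change of SAP wording and re-derivation of one variable from data already held. The downside is that co-infections acquired after onset are not studied in the GEE.

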### 9.5.3 Analysis of time to first detected incident cervical HPV infections

|                                                           | Covariates                                       | Type    | Categories                                               | Time-dependent | Comment                      |
|-----------------------------------------------------------|--------------------------------------------------|---------|----------------------------------------------------------|----------------|------------------------------|
| Demographic characteristics
(defined at subject level) | Region                                           | Class   | Europe
Asia Pacific
Latin America
North America | No             |                              |
| Behavioral Covariates
(defined at subject level)       | Smoking                                          | Ordinal | [0-0.5[ pack/year
≥0.5 pack/year                      | No             |                              |
|                                                           | Age at beginning of sexual activity (years)      | Ordinal | Never had sexual intercourse
<15
15-17
18-25    | No             |                              |
|                                                           | Number sexual partner during the previous year   | Ordinal | 0
1
2-3
≥4                                      | No             |                              |
|                                                           | Marital status                                   | Binary  | Living or lived with a partner
Single                 | No             | Re-assessed at yearly visits |
|                                                           | At least one previous pregnancy                  | Binary  | No
Yes                                                | No             | Re-assessed at each visit    |
|                                                           | Hormones for contraception or another indication | Binary  | No
Yes                                                | No             | Re-assessed at each visit    |
|                                                           | Intra-uterine device                             | Binary  | No
Yes                                                | No             | Re-assessed at each visit    |
|                                                           | Sterilized                                       | Binary  | No
Yes                                                | No             | Re-assessed at each visit    |
|                                                           | Chlamydia trachomatis                     | Binary  | No
Yes                                                | No             | Re-assessed at each visit    |

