**Figure 1 Study Overview**

[figure not shown]

- **Experimental design:** A phase III, controlled, multi-center (n=135), and multi-country (n=14) study with two parallel groups.
- **Treatment Groups:** 2 groups: vaccine and control
  - Vaccine: 20µg HPV-16 L1 VLP/20µg and HPV-18 L1 VLP/50µg MPL®/ 500µg aluminum in the form of Al(OH)3,
  - Control: Hepatitis A vaccine (Havrix™-based investigational formulation) (720 ELISA units of antigen; 500µg aluminum in the form of Al(OH)3).
- **Treatment allocation:** Randomized (1:1).

- **Randomization method:** SBIR (Internet randomization).
- **Blinding:** Double-blind.
- **Enrolment period:** May 2004 to June 2005.
- **Study regions:** Asia Pacific, Europe, Latin America and North America.
- **Enrolled:** 18729 subjects aged 15-25 years. Total Vaccinated Cohort (TVC): 18644 subjects. Total Vaccinated Cohort for efficacy 1 (TVC-1): 18525 subjects.
- **Control arm** (HAV vaccine group): TVC: 9325 subjects. TVC-1: 9267 subjects.
- **Vaccination schedule(s):** Three doses of HPV vaccine or HAV vaccine (control arm) administered on a Month 0, 1, 6 schedule.
- **Study visits:** 10 study visits per subject scheduled at Months 0, 1, 6, 7, 12, 18, 24, 30, 36 and 48.
- **Total duration of the study:** 48 months of follow-up from study entry planned for all subjects.
- **Database freeze for the final analysis:** October 2008; **Database freeze for the M48 analysis:** March 2010.

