#### 4.4.4 Other determinants

The following analysis factors will be defined at subject level using data from the CRF:

- Age groups (years) at the start date of time to event for each endpoint (cf. Section 8.5 for more details). This determinant will be analyzed primarily as a continuous variable. For exploratory purposes, it could also be categorized as followed: 15-17; 18-25.
- Geographical regions: Europe (Belgium, Finland, Germany, Italy, Spain, UK); Asia Pacific (Australia, Philippines, Taiwan, Thailand); Latin America (Brazil, Mexico); North America (Canada, United States).

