### **6.2.7 Analysis of time to first detected cervical HPV infections**

#### **6.2.7.1 Population**

The population for the analysis of time between the start of sexual activity and a first detected incident cervical HPV infection (or a first confirmed 6-month cervical HPV infection) will be restricted to subjects from the TVC-1-Control arm cohort for whom the date of start of sexual activity is known (i.e. either collected or computed, so that a starting date is available for the computation of the time between the start of sexual activity and a first detected cervical HPV infection) and for whom the date of start of sexual activity is either less than 6 months prior to their inclusion in the study or during the follow-up period.

Subjects with cervical HPV infections preceding the start of sexual activity will not be taken into account in the analyses.

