### 6.2.7.4 Time computation

The time to a first detected incident cervical HPV infection (or a first confirmed 6-month cervical HPV infection) following the start of sexual activity will be calculated in days as: Date of event or Date of censoring - Date of start of sexual activity.

The date of start of sexual activity will be determined as follows:

- For subjects who already had sexual intercourse prior to study entry: the date of start of sexual activity will correspond to the birthdate collected in the CRF plus the age at first sexual intercourse collected in the baseline behavioral questionnaire,.
- For subjects who did not have sexual intercourse prior to study entry: the date of start of sexual activity will correspond to the maximum between i) the date of the yearly questionnaire in which subjects reported having first sexual intercourse (or the date of the visit corresponding to the yearly questionnaire if the date of the questionnaire is missing) and ii) the date of the preceding detected cervical HPV infection, minus the date of the preceding questionnaire (or visit), divided by 2. In case there is no preceding questionnaire (i.e. baseline questionnaire is missing and first sexual intercourse is reported in the 1-year questionnaire), the date of start of sexual activity will be equal to the date of the 1-year questionnaire (or visit) minus 6 months.

The date of event will be:

- the date of the detection of the first incident cervical HPV infection (or the date of onset or the first confirmed 6-month cervical HPV infection) during the 48-month follow-up period,

The date of censoring will be:

- the date of Month 48 visit for cervical HPV infections of subjects who attended all visits during the 48-month follow-up period and did not have any cervical HPV infection during this period,
- the date of the last PCR reported at the latest visit for which data are available or the date of the last cytology (if the date is after the date of the last PCR) for cervical HPV infections of subjects who did not attend all visits during the 48-month follow-up period and who did not have any cervical HPV infection throughout their follow-up period (from first to last visit).

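### Section 4.4.4 wants age at time zero continuous, but the first-infection tables (9.5.3, 9.5.4) enter age at sexual debut in levels that come down to roughly one cut at 18

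*SAP*

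**What the plan says.** - **Age determinant (SAP 4.4.4).** Age is defined as "Age groups (years) at the start date of time to event for each endpoint (cf. Section 8.5 for more details"). The annex meant is now numbered 9.5. On scale: "This determinant will be analyzed primarily as a continuous variable". The categories come second: "For exploratory purposes, it could also be categorized as followed: 15-17; 18-25".
- **Time zero (SAP 6.2.7.4).** Time to first incident or first 6-month persistent infection is "Date of event or Date of censoring - Date of start of sexual activity".
- **Population (SAP 6.2.7.1).** The debut date must be known and must fall "either less than 6 months prior to their inclusion in the study or during the follow-up period". The parent trial enrolled "18729 subjects aged 15-25 years" and planned 48 months of follow-up (SAP 3.1).
- **Covariate lists (SAP 9.5.3 and 9.5.4).** The only age row in each table is "Age at beginning of sexual activity (years"), typed as ordinal, with the levels Never, <15, 15-17 and 18-25. Section 4.4.3 gives the same four levels.
- **Related text.** Section 6.1.2 points to this annex for the determinants used, allows documented recoding at analysis, and lets the Never level be left out. Section 6.2.7.5 reuses the models of 6.2.4.5, which name age at study entry as an example covariate.

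**The concern.** For these two endpoints, age at the start of the clock and age at debut are one quantity. Section 4.4.4 gives it a continuous scale and the annex gives it levels. An analyst cannot follow both with a single age term. Following the annex turns a coding that 4.4.4 reserves for exploration into the model coding.

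Two things are at stake. Pooling 15 with 17, and 18 with 25, discards information on the age effect. It also leaves residual confounding by age in the hazard ratios of the other determinants, since the multivariable model adjusts each determinant for the rest. Separately, the printed levels stop at 25, although debut during follow-up can come later.

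**Working it through.** The SAP states no information or power figure on this point, so there is none to reproduce. The check has three steps.

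**1. Which levels can be filled.** Inputs: entry age 15-25, debut less than 6 months before entry or later, 48 months of follow-up.

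- *<15.* Entry is at 15.0 or later, so debut must fall after 15.0 − 0.5 = 14.5 years, and the level needs entry before 15.5. For women with intercourse before entry, 6.2.7.4 sets the debut date to birthdate plus reported age. If age is recorded in whole years (an assumption), a report of 14 puts debut at least 15 − 14 = 1 year before entry. That fails the 6-month rule, so the level is empty. If fractional ages are recorded, the selection model in step 3 puts about 0-1.5% of women there.
- *Never.* This conflicts with having a debut date. It could arise only by lag, because 4.4.3 takes the value from the last questionnaire before the infection.
- *Above 25.* Entry at 25 plus 4 years of follow-up reaches 29, and 26-29 has no level.

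What is left is 15-17 versus 18-25.

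**2. Information kept by one cut at 18.** Near the null, Cox information is proportional to covariate variance. With a linear log-hazard effect, the share kept is the squared correlation between age and the indicator of age 18 or over: p(1−p) × (difference in mean age between the groups)² / variance of age, where p is the share under 18.

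- Uniform 15-25: p = 0.3, means 16.5 and 21.5, variance 100/12 = 8.33. Kept: 0.3 × 0.7 × 5² / 8.33 = 0.63, a loss of 37%.
- Uniform 15-29: p = 3/14, means 16.5 and 23.5, variance 196/12 = 16.33. Kept: 0.168 × 7² / 16.33 = 0.505, a loss of about 50%.
- Uniform 15-21: p = 0.5, means 16.5 and 19.5, variance 36/12 = 3. Kept: 0.25 × 3² / 3 = 0.75, a loss of 25%.

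**3. Other assumed shapes, same formula.**

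| Assumed debut-age distribution | Loss |
|---|---|
| 15 + exponential, mean excess 2-5 years | 34-41% |
| Normal, mean 18, SD 1-3, truncated to 15-30 | 35-39% |
| Normal, mean 19, SD 1.5-3, truncated to 15-30 | 44-46% |
| Entry age uniform 15-26, 6-month rule applied, latent debut mean 16-18 | 35-52% |
| Same, latent debut mean 19 | 56-59% |

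If few women start before 18 the loss is larger: 87% for a normal with mean 20 and SD 1, where 2% are under 18. A rough Cox simulation (60 replicates) gave a loss of about 31% where the formula gave 37-38%, so the formula may overstate the loss somewhat.

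The share with debut at 26 or later is 0-2% for the truncated normals tried (means 17-20), 0-6% for the exponentials, and 3/14 = 21% if uniform to 29.

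**The case against.** The strongest reply is that 4.4.3 and 4.4.4 define two determinants, and that the 4.4.4 age has no row in any annex table, 9.5.1 and 9.5.2 included. Its absence from 9.5.3 and 9.5.4 would then be a general omission and not a decision to categorise. A continuous age could still enter under 4.4.4, or as age at study entry through 6.2.4.5. This stands to the extent that the loss is not certain to occur. It does not remove the conflict. Section 6.1.2 presents the annex as the list of determinants used. Adding the 4.4.4 age would put one quantity in the model twice, once continuous and once cut. Age at study entry is a further version, which can differ from age at time zero by up to four years for women who start during follow-up.

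A second reply is that 6.1.2 allows documented recoding, both when a category is sparse and when another form is more meaningful. That is correct, so the coding is not locked in. But it leaves the form of the age term to be chosen at analysis, although 4.4.4 has already chosen it.

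Third, the two ages are not identical in every record: the questionnaire value can lag, and time zero for follow-up starters is interpolated. This is a reason to tie the covariate to the date used as time zero.

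Two stronger readings should be resisted. A reader might infer that 4.5.2 removes women with debut after 25. That section excludes missing or inconsistent values, and a known age of 27 is neither; the SAP simply does not say how such women enter. A reader might also convert the information loss into lost power, but the SAP makes no power claim for this determinant.

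**Conclusion.** The conflict between 4.4.4 and Tables 9.5.3 and 9.5.4 holds on the SAP's own text. Followed literally, the tables reduce debut age to essentially the split that 4.4.4 calls exploratory, and they leave debut at 26-29 undefined.

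The loss of about 25-59% is illustrative. It rests on assumed debut-age distributions and a linear log-hazard effect, and the SAP supplies neither, so no single percentage or narrower range can be read from it. That <15 is strictly empty depends on whole-year recording; otherwise it is nearly empty. The point concerns one covariate in two secondary analyses that go into a stand-alone report. It should be corrected because the plan already contains the better rule.

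**What to change.** - In 9.5.3 and 9.5.4, replace the ordinal row by one continuous term: age in years at the debut date used as time zero. Check linearity, with a spline or quadratic term if it fails.
- State that no second age term for the same quantity is added, and say how the age at study entry named in 6.2.4.5 applies to these two analyses.
- Keep 15-17 and an open-ended 18-and-over group for Kaplan-Meier curves and descriptive tables, so that every included woman aged 15 or over at debut has a level.

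The cost is SAP wording only. The small downside is a hazard ratio per year of age in place of category contrasts.
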